***Secondary endpoints***

The duration of hospital stay from the time of randomization.The number of ventilator-free days during the first 28 days following randomization.The time to (all-cause) death following the first 10, 28, and 56 days since randomization.The WHO ordinal outcome scale for COVID-19 at days 28, 42 and 56
^24^.Fever clearance time (defined as temperature <37.5°C for 48 hours).Development of acute respiratory distress syndrome (ARDS) defined by the Kigali criteria
^25^.Oxygenation-free days over the first 28 days.Risk of serious adverse events (SAEs).Risk of grade 3 or 4 adverse events (AEs).

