### Safety reporting

The safety profile of chloroquine is well understood and the risks related to chloroquine phosphate/sulphate/hydrochloride are very low, unless the drug is taken in overdose
^28^. Most side effects are infrequent. Adverse reactions (ARs) relating to the cardiovascular system, the central nervous system, the skin, hypoglycaemia, hypersensitivity, gastrointestinal, and retinal toxicity have all been described, though usually after high doses and protracted exposures. The main adverse effect is itching in dark-skinned individuals; Africans are much more commonly affected compared to Asians. Adverse effects will be classified and graded according to the Common Terminology Criteria for Adverse Events (CTCAE) system
^29^. All serious and grade 3 or 4 AEs will be compared between arms and reported by frequency per arm. An independent DMC will oversee the safety of the trial participants.

***Definitions***. The definitions of the principles of International Conference on Harmonization (ICH) Good Clinical Practice (GCP) apply to this trial protocol (see
Table 4).

**Table 4. T4:** International Conference on Harmonization (ICH) Good Clinical Practice (GCP) definitions.

Table	Definition
Adverse event (AE)	Any untoward medical occurrence in a participant or clinical trial subject to whom an investigational medicinal product has been administered including occurrences that are not necessarily caused by or related to that product.
Adverse reaction (AR)	Any untoward and unintended response to an investigational medicinal product related to any dose administered.
Unexpected adverse reaction (UAR)	An AR, the nature or severity of which is not consistent with the information about the investigational medicinal product in question set out in the Summary of Product Characteristics (SPC) for that product.
Serious adverse event (SAE) or serious adverse reaction (SAR) or suspected unexpected serious adverse reaction (SUSAR)	Respectively any AE, AR or UAR that: Results in death Is life-threatening * Requires hospitalisation or prolongation of existing hospitalisation ** Results in persistent or significant disability or incapacity Consists of a congenital anomaly or birth defect Is another important medical condition ***

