^*^ The term life-threatening in the definition of a serious event refers to an event in which the participant is at risk of death at the time of the event; it does not refer to an event that hypothetically might cause death if it were more severe, for example, a silent myocardial infarction.

^**^ Hospitalisation is defined as an inparticipant admission, regardless of length of stay, even if the hospitalisation is a precautionary measure for continued observation. Hospitalisations for a pre-existing condition (including elective procedures that have not worsened) do not constitute an SAE.

^***^ Medical judgement should be exercised in deciding whether an AE or AR is serious in other situations. The following should also be considered serious: important AEs or ARs that are not immediately life-threatening or do not result in death or hospitalisation but may jeopardise the subject or may require intervention to prevent one of the other outcomes listed in the definition above.

AEs include:
An exacerbation of a pre-existing illnessAn increase in frequency or intensity of a pre-existing episodic event or conditionContinuous persistent disease or a symptom present at baseline that worsens following administration of the study intervention

ARs include any untoward or unintended response to drugs. Reactions to the trial treatment (chloroquine) or comparator should be reported appropriately.

In the context of this trial AEs do not include:
Medical or surgical procedures; the condition that leads to the procedure is the AEPre-existing disease or a condition present before treatment that does not worsenHospitalisations where no untoward or unintended response has occurred, e.g. elective cosmetic surgery, social admissionsOverdose of medication without signs or symptoms

Death should always be reported as a SAE, regardless of cause.

***Assessment of AEs***. All grade 3 or 4, or SAEs and SARs, whether expected or not, should be recorded in the CRF. Non-serious grade 1 or 2 AEs need not be recorded unless they are thought to be related to the trial treatment or they result in a change or interruption in treatment.

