The frequency of serious and grade 3 and 4 ARs as well as the frequency of specific AEs will be summarized (both in terms of the total number of events as well as the number of participants with at least one event). The proportion of participants with at least one such event (overall and for each specific event separately) will be summarized and (informally) compared between the two treatment groups based on Fisher’s exact test if the expected number in one of the cells is at most one and the chi-square test if expected number in each cell is larger than one.

Analysis of other secondary outcomes

1. The duration of hospital stay from the time of randomization.2. The number of ventilator-free days during the first 28 days following randomization.3. The time to (all-cause) death following the first 10, 28, and 56 days since randomization.4. The WHO ordinal outcome scale for COVID-19 at days 28, 42 and 56
^24^.5. Fever clearance time.6. Development of ARDS defined by the Kigali criteria
^25^.7. Oxygenation-free days over the first 28 days.

The analyses of these secondary endpoints will be defined in the statistical analysis plan.

***Statistical hypotheses***. The primary null hypothesis is that the rate of clearance of virus from throat/nose swabs is not different between chloroquine compared with standard of care therapy.

***Analysis datasets***. The primary analysis population for all analysis is the full analysis population containing all randomized participants except for those mistakenly randomized without COVID-19. Participants will be analysed according to their randomized arm (intention-to-treat). In addition, the primary endpoint will be analysed on the per-protocol population, which will exclude the following participants: major protocol violations and those receiving less than one week of administration of chloroquine for reasons other than death.

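### The Statistics section compares serious and grade 3/4 adverse reactions between arms, where the endpoints call for all-cause adverse events; reactions are tied to chloroquine, which controls do not receive

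*Protocol article*

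**What the plan says.** The protocol article describes the safety comparison in several places, and they do not agree.

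- **Statistics, Secondary endpoints, AEs:** "The frequency of serious and grade 3 and 4 ARs as well as the frequency of specific AEs will be summarized". The proportion with at least one such event is "overall and for each specific event separately) will be summarized and (informally) compared between the two treatment groups based on Fisher’s exact test" if an expected cell count is at most one, and otherwise on the chi-square test.
- **Endpoints, Secondary endpoints:** the list has the risk of SAEs and "Risk of grade 3 or 4 adverse events (AEs". No causality condition is attached.
- **Safety reporting (opening paragraph):** "All serious and grade 3 or 4 AEs will be compared between arms and reported by frequency per arm".
- **Safety reporting (DMC paragraph):** the interim report summarises SAEs and grade 3 and 4 AEs by arm.

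The two terms have different definitions. Table 4 defines an AR as "Any untoward and unintended response to an investigational medicinal product related to any dose administered". Under Causality, serious events are judged against chloroquine. Those rated possible, probable or definite become serious adverse reactions (SARs); those rated unrelated or unlikely stay SAEs.

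On recording, Assessment of AEs requires every grade 3/4 and serious event to go into the CRF. For milder events the rule is: "Non-serious grade 1 or 2 AEs need not be recorded unless they are thought to be related to the trial treatment", with a second trigger if the event leads to a change or interruption in treatment.

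**The concern.** Defining the safety profile of chloroquine is a stated secondary objective. The trial is open label and the control arm receives standard of care without chloroquine or placebo. An event class that requires a causal link to chloroquine can therefore be filled freely in one arm and hardly at all in the other. A between-arm test on that class measures attribution by unblinded investigators as much as it measures harm. It also leaves out of that line every serious event in the chloroquine arm judged unrelated or unlikely.

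A related problem affects the tests of each specific event, which carry no grade limit. One of the two triggers for recording a non-serious grade 1–2 event is suspected relation to trial treatment. That trigger can hardly operate in controls, so these tests may mix events captured alike in both arms with events captured mainly in one.

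**Working it through.** **Inputs from the protocol article.** Total enrolment is 240 (Sample size calculation) with 1:1 allocation (Randomization and treatment allocation), so n = 240/2 = 120 per arm. The test rule is Fisher's exact test if an expected cell is at most one, otherwise chi-square. The article gives no expected adverse event rate and no power for safety, so there is no stated figure to reproduce.

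**Assumptions.** A two-sided 0.05 threshold and a chi-square test without continuity correction; the article states neither for this comparison.

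**Step 1: which test applies.** With x participants having an AR on chloroquine and none in control, the smallest expected count is x/2. For x = 2 it is 1, so Fisher applies. For x of 3 or more it exceeds 1, so chi-square applies.

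**Step 2: the p-value for x v 0.** For a 2×2 table with a zero cell and n per arm, the Pearson statistic reduces to X² = 2n·x/(2n − x).

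- x = 2: Fisher p = 0.498
- x = 3: 240·3/237 = 3.04, p = 0.081
- x = 4: 240·4/236 = 4.07, p = 0.044
- x = 6: 240·6/234 = 6.15, p = 0.013

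Four participants with an attributed event are enough to cross 0.05. The choice of test matters. With a continuity correction, 4 v 0 gives 0.130, 5 v 0 gives 0.071 and 6 v 0 gives 0.039. If Fisher were used throughout, the values would be 0.122, 0.060 and 0.029. Either way the crossing point moves from four to six.

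**Step 3: how often this happens with no true difference.** Assume the same true risk p of a serious or grade 3/4 event in both arms, a share q of chloroquine-arm events judged at least possibly related, and no ARs in control. The number with an AR on chloroquine is then binomial(120, p·q). From Step 2, the chance of p<0.05 is the probability that this number is 4 or more. The column for all-cause AEs applies the same test rule to both arms at risk p.

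| Assumed true risk, both arms | All-cause AEs | ARs, q = 10% | ARs, q = 25% | ARs, q = 50% |
|---|---|---|---|---|
| 5% | 4.8% | 0.3% | 6.4% | 35.3% |
| 10% | 5.2% | 3.3% | 35.3% | 85.6% |
| 20% | 5.1% | 22.0% | 85.6% | 99.8% |

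The all-cause comparison holds its nominal level throughout. The AR comparison ranges from below the nominal level to near certainty, driven by p·q. The values of p and q are illustrative; the article gives none.

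**Step 4: is the analysis left to the SAP?** The Statistics section lists seven other secondary outcomes whose analyses the SAP will define. SAEs and grade 3/4 AEs are not among them. Their analysis is the one fixed in the AEs paragraph.

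**The case against.** The strongest reply is that ARs is a slip for AEs. The paragraph sits under the heading AEs, the same sentence goes on to specific AEs, and three other places in the article specify AEs. That is a plausible reading. It supports making the correction, because the paragraph as written is the one that fixes the analysis and AR is a defined term with a different meaning.

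Several stronger readings are tempting, and the article does not support them.

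- *The all-cause comparison has been abandoned.* The endpoint list, the Safety reporting section and the DMC report all commit to it. The fault is a contradiction between sections.
- *Control counts are near zero across the whole safety analysis.* Every serious and grade 3/4 event is recorded in both arms whatever its cause. Only the AR line, and in large part the grade 1–2 events, are affected.
- *Controls cannot have an AR at all.* The notes to Table 4 are looser than the table: "ARs include any untoward or unintended response to drugs", and reactions to the comparator are also to be reported. A few control ARs are conceivable, although this wording conflicts with Table 4 and with causality being judged against chloroquine.
- *Controls cannot have an AE.* Table 4 does refer to participants "to whom an investigational medicinal product has been administered", but it is presented as a set of ICH GCP definitions, and the explicit between-arm comparison of AEs shows that controls are counted.
- *Grade 1–2 events are recorded only if drug-related.* A change or interruption in treatment is a second trigger.
- *The test is bound to show excess harm.* At a 5% risk with 10% of events attributed, the chance is 0.3%.

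It is also fair to say that the comparison is labelled informal, and that stopping for harm rests on the DMC's judgement, so no decision rule depends on this test. That limits the consequence for trial conduct. It does not protect the published safety comparison.

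**Conclusion.** The point stands as an internal contradiction with a material effect on the safety analysis. The Statistics section fixes the between-arm comparison on ARs, while the endpoints, the Safety reporting section and the DMC report specify AEs. If it is followed literally, the comparison is biased towards showing harm, because one arm has few or no events by definition. Four v none of 120 per arm is enough for p=0.044 under the plan's rule (uncorrected chi-square). The practical size depends on the true event risk and on the attribution share, neither of which the article gives; over the illustrated range the chance of a spurious p<0.05 runs from 0.3% to 99.8%, assuming no control ARs.

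The grade 1–2 point is narrower: tests of specific AEs that include these grades are subject to differential capture. Its size cannot be estimated from the article, which also does not say whether specific AEs is meant to include grades 1–2.

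**What to change.** In the AEs paragraph of the Statistics section:

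1. Replace ARs with AEs, and state that this means all serious and grade 3/4 events whatever the cause, counted from randomisation, in both arms.
2. Report relatedness to chloroquine descriptively, without a between-arm test.
3. Base between-arm tests of specific events on serious and grade 3/4 AEs. Describe grade 1–2 events and flag them as differentially ascertained.

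The CRF already captures all serious and grade 3/4 events without a causality condition, so no new data are needed. The cost is wording, and the change should be made before the SAP is completed.

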A laboratory abnormality must be recorded as a clinical AE only if it is associated with an intervention. Intervention includes, but is not limited to, discontinuation of a current treatment, dose reduction/delay of a current treatment, or initiation of a specific treatment. In addition, any medically important laboratory abnormality may be reported as an AE at the discretion of the investigator. This would include a laboratory result for which no intervention is needed, but the abnormal value suggests a disease or organ toxicity. Laboratory events will be graded according to CTCAE definitions.

Seriousness

When an AE or AR occurs, the investigator responsible for the care of the participant must first assess whether or not the event is serious using the definition given in
Table 4. If the event is serious and not only related to COVID-19, or is fatal, then an SAE Form must be completed and the OUCRU clinical trials unit (CTU) notified within 24 hours.

Severity or grading of AEs

The severity of all AEs and/or ARs (serious and non-serious) in this trial should be graded using the toxicity gradings in Toxicity grading and management (CTCAE)
^29^.

Causality

The investigator must assess the causality of all serious events or reactions in relation to the trial therapy (chloroquine) using the definitions in
Table 5. There are five categories: unrelated, unlikely, possible, probable, and definitely related. If the causality assessment is unrelated or unlikely to be related, the event is classified as an SAE. If the causality is assessed as possible, probable or definitely related, then the event is classified as an SAR.

**Table 5. T5:** Assigning type of SAE through causality.

Relationship	Description	SAE type
Unrelated	There is no evidence of any causal relationship	Unrelated SAE
Unlikely	There is little evidence to suggest that there is a causal relationship (for example, the event did not occur within a reasonable time after administration of the trial medication). There is another reasonable explanation for the event (for example, the participant’s clinical condition, other concomitant treatment).	Unrelated SAE
Possible	There is some evidence to suggest a causal relationship (for example, because the event occurs within a reasonable time after administration of the trial medication). However, the influence of other factors may have contributed to the event (for example, the participant’s clinical condition, other concomitant treatments).	SAR

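### The safety endpoints are serious and grade 3 or 4 adverse events, but the analysis sentence compares adverse reactions, which the control arm can hardly have

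*Protocol article*

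**What the plan says.** The list of secondary endpoints includes "Risk of serious adverse events (SAEs") and "Risk of grade 3 or 4 adverse events (AEs"). Neither carries a causality condition. The opening paragraph of Safety reporting commits to the matching comparison: "All serious and grade 3 or 4 AEs will be compared between arms and reported by frequency per arm".

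In the Statistics section, under the subheading for AEs, the counted quantity changes: "The frequency of serious and grade 3 and 4 ARs as well as the frequency of specific AEs will be summarized". The next sentence sets the test: "The proportion of participants with at least one such event (overall and for each specific event separately) will be summarized and (informally) compared". The arms are tested with Fisher's exact test or chi-square according to the expected cell count.

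The article separates the two terms. Table 4 defines an adverse reaction as "Any untoward and unintended response to an investigational medicinal product related to any dose administered". On causality, "The investigator must assess the causality of all serious events or reactions in relation to the trial therapy (chloroquine"), and "If the causality is assessed as possible, probable or definitely related, then the event is classified as an SAR". The control arm is standard of care without chloroquine, and the trial is open label (Study design).

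**The concern.** Randomisation supports a comparison of all events, because both arms can have them and neither count needs a judgement about cause. It does not support a comparison of events attributed to a drug that only one arm receives. If the analysis sentence is followed as written, the chloroquine figure is an unblinded investigator's attribution count, set against a control figure that is close to zero by construction. A difference would then say little about whether chloroquine causes harm. Equal risk could look like excess harm, and harm put down to COVID-19 would drop out of the overall reaction count.

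This is not a detail left for the analysis plan. The article lists the other secondary outcomes whose analysis that plan will define, and the two safety endpoints are not among them. The sentence in Statistics is the only text that says how they will be analysed. Safety is named in the stated aim of the study, and the safety profile is a secondary objective.

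**Working it through.** No stated figure is in dispute, so the check is first a comparison of texts and then a calculation of the consequence.

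**Texts side by side**

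| Place in the protocol article | Quantity | Causality condition |
|---|---|---|
| Secondary endpoints | SAEs; grade 3 or 4 AEs | none |
| Safety reporting, opening paragraph | serious and grade 3 or 4 AEs, compared between arms | none |
| Safety reporting, reports to the data monitoring committee | SAEs and grade 3 and 4 AEs by arm | none |
| Statistics, AEs | serious and grade 3 and 4 ARs, plus specific AEs | yes for the ARs, none for the specific AEs |

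For a serious event, classification as a reaction requires at least a possible relation to chloroquine. For a non-serious grade 3 or 4 event, the Table 4 definition requires a response to the investigational product. On either route a participant who never received chloroquine has essentially no way to qualify. The exception is the looser sentence after Table 4, which counts responses to drugs in general and mentions reactions to a comparator.

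**Inputs for the calculation**

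- 240 participants (Sample size calculation) at 1:1 (Randomization and treatment allocation), so 120 per arm.
- Test rule from Statistics: Fisher's exact test if an expected count is at most 1, otherwise chi-square (taken here without continuity correction).
- Control count of reactions: 0, from Table 4 and the causality rule.
- Assumed, because the documents give neither: the true event risk, equal in both arms, and the share of chloroquine-arm participants with an event whose event is called related.

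**The test against zero.** With x participants on chloroquine and 0 on control, the smaller expected count is x/2, so chi-square applies from x = 3. The statistic is 240 × (120x)² / (120 × 120 × x × (240 − x)) = 240x / (240 − x).

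- x = 3: 720/237 = 3.04, p = 0.081
- x = 4: 960/236 = 4.07, p = 0.044
- x = 8: 1920/232 = 8.28, p = 0.004

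Four attributed cases are therefore enough for p<0.05.

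**Chance of a spurious result under equal true risk.** With event risk r and attributed share s, the chloroquine count is binomial(120, r × s), and the chance of p<0.05 is P(X ≥ 4):

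| True risk in both arms | s = 10% | s = 20% | s = 30% | s = 50% |
|---|---|---|---|---|
| 5% | 0.3% | 3.3% | 10.7% | 35.3% |
| 10% | 3.3% | 22.0% | 48.7% | 85.6% |
| 20% | 22.0% | 71.1% | 93.4% | 99.8% |
| 30% | 48.7% | 93.4% | 99.6% | about 100% |

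**Same rule, events counted regardless of cause.** At equal true risks of 5%, 10%, 20% and 30%, the chance of p<0.05 is 4.8%, 5.2%, 5.1% and 5.0%. The test rule is sound in this setting. The fault lies in the quantity put into it.

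**The case against.** The strongest reply is that this is a slip of one letter. The subheading says AEs, the same sentence goes on to specific AEs, and the endpoint list, the safety section and the data monitoring committee's reports all use AEs. That is quite possibly right. It does not remove the point, because the slip would sit in the operative analysis sentence, and the article gives AR a distinct meaning elsewhere.

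Three further objections limit the point, and they stand.

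- A reader might infer that the control arm scores zero by definition, or that it is a no-drug arm. Table 4 and the causality rule point to zero, but the looser sentence on drugs and comparator leaves room for a control reaction. Control participants also receive standard of care; what they lack is chloroquine. The accurate statement is that controls essentially cannot score under the main definitions and that the article is inconsistent on what a reaction is.
- A reader might infer that real harm would vanish. For example, 24 against 12 participants with a serious event (p = 0.030) would become 0 against 0 if every event were attributed to COVID-19. That holds only for the overall reaction line. Specific AEs are still compared between arms with no causality condition, the safety section still commits to comparing all serious and grade 3 or 4 AEs, the data monitoring committee sees AEs by arm, and survival is analysed for all causes.
- The comparison is labelled informal and the endpoints are secondary. No decision rule hangs on these p-values, and stopping for harm rests on the committee's judgement.

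**Conclusion.** The contradiction is real and should be corrected. The endpoints and the promised comparison are adverse events regardless of cause, while the only analysis text for them counts adverse reactions. As written, the informal test on reactions is uninterpretable, because it sets an open-label attribution count against a control count that is essentially fixed at zero.

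The size cannot be pinned down. Across the assumed grid the chance of a spurious p<0.05 runs from 0.3% to nearly 100%, against about 5% when all events are counted. The calculation assumes 120 analysed per arm, a control count of exactly zero, and the stated risks and shares. The contradiction between the texts depends on none of these.

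The point does not extend to the comparison of specific AEs, to interim safety monitoring or to the primary virological analysis.

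**What to change.** In Statistics, under AEs, change the quantity compared between arms from serious and grade 3 and 4 ARs to serious and grade 3 or 4 AEs, regardless of causality, in both arms. Report ARs and SARs for the chloroquine arm descriptively, without a test. Reconcile the looser sentence on reactions to drugs or comparator with Table 4, so that the article has one definition of an adverse reaction. Naming both arms explicitly also helps because Table 4's definition of an adverse event can be read as limited to people who received the investigational product.

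The cost is a wording change, carried into the statistical analysis plan before database lock. No new data are needed: the section on assessment of AEs already requires all grade 3 or 4 events and all SAEs on the case report form.

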### Eligibility criteria

***Inclusion criteria***.

Laboratory-confirmed SARS-CoV-2 infection as determined by RT-PCR, or other commercial or public health assay in any specimen <48 hours prior to randomization, and requiring hospital admission in the opinion of the attending physician.Provides informed consent prior to initiation of any study procedures (or consent provided by an authorized representative).Understands and agrees to comply with planned study procedures.Agrees to the collection of oropharyngeal (OP) swabs and venous blood per protocol.Male or female adult ≥18 years of age at time of enrolment.

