***Regulatory reporting***. All SAEs will be reported as soon as possible to the MoH ethics committee. An initial written report of an SAE resulting in death, or that is life threatening, has to be reported urgently within seven working days of the study team becoming aware of the SAE. Other SAEs must be reported within 15 working days of the study team becoming aware of the SAE. Additional medical information of the SAE’s development must be reported in an additional report until the trial participant recovers or stabilizes without further changes expected. The format and content of the initial report should follow the Vietnam MoH EC report template and include all information available at the time of reporting. All SAEs will be reported to OxTREC in the annual review form and to the DMC in accordance to the DMC charter.

***Safety reporting***. An independent DMC will oversee the safety of the trial. A DMC Charter will describe the membership of the DMC, relationships with other committees, terms of reference, decision-making processes, and the approximate timing and frequency of interim analyses (see
*Extended data*
^27^). At the interim analyses, the DMC will receive a report including summaries of mortality, SAEs, grade 3 and 4 AEs, and the time to viral clearance (defined as the time following randomization until the midpoint between the last positive and the first of the negative throat/nose swabs) by treatment arm. The report will be prepared by the study statistician and distributed to all DMC members for review. Based on these data, the committee will make recommendations on the continuation, cessation or amendment of the study.

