The DMC will perform a first safety analysis after the first 10 participants from the pilot study have completed the allocated two-week treatment or died. A second and a third interim safety analysis will be performed assessing safety, efficacy and futility, after 60 and 120 participants have completed the allocated two-week treatment or died. Stopping for harm of chloroquine will be considered if a safety issue emerges which is sufficiently large, in the judgement of the DMC, to suggest that continued exposure of participants to the drug is unethical. Early stopping for efficacy is not foreseen, as this is a study with a virological rather than survival endpoint. However, if chloroquine truly appears to have an extraordinary beneficial effect then the DMC will be able to recommend this to the TSC. The DMC will be able to mandate additional safety analyses at any time point they deem fit.

As the dissemination of preliminary summary data could influence the further conduct of the trial and introduce bias, access to interim data and results will be confidential and strictly limited to the involved statistician and the monitoring board and results (except for the recommendation) will not be communicated to the outside and/or clinical investigators involved in the trial. Further reviews will be at the discretion of the DMC. All DMC reports, replies or decisions will be sent to the responsible research ethical committees.

***Protocol violations***. A protocol deviation is any non-compliance with the clinical trial protocol or GCP requirements. If such a deviation results in an impact on patient safety or scientific integrity it becomes a protocol violation. The non-compliance may be either on the part of the participant, the investigator, or the study site staff. Whenever violations occur, corrective actions are to be developed by the site and implemented promptly. It is the responsibility of the site investigators to use continuous vigilance to identify and report protocol deviations and violations. All deviations and violations must be documented in source documents and reported to the OUCRU CTU within two days of being identified. In addition, protocol violations must be reported to the relevant ethics committees.

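### As worded, the main adverse event comparison would omit any patient mistakenly randomised without COVID-19, even one who took chloroquine

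*Protocol article*

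**What the plan says.** Under Statistics, Analysis datasets, the protocol article sets one population: "The primary analysis population for all analysis is the full analysis population containing all randomized participants except for those mistakenly randomized without COVID-19". Participants are analysed in the arm to which they were randomised. The only other population is per-protocol, and it serves the primary endpoint alone. The article defines no safety or as-treated population.

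The adverse event analysis stands in the same Statistics section. Proportions of participants with at least one event "will be summarized and (informally) compared between the two treatment groups", using Fisher's exact test or the chi-square test. Seven other secondary outcomes are listed there as deferred to the statistical analysis plan. Adverse events are not among them.

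The Safety reporting section says: "All serious and grade 3 or 4 AEs will be compared between arms and reported by frequency per arm". The risks of serious adverse events and of grade 3 or 4 adverse events are both listed as secondary endpoints.

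**The concern.** Leaving out a patient who never had the infection is defensible for viral clearance, because there is no virus to clear. That reason does not carry over to harms. Whoever swallows the drug is at risk of drug toxicity, infected or not. A rule written for efficacy has been extended to safety by the words covering all analyses.

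What is at stake is the completeness of one table, more than the oversight of patients. Serious events in such a patient keep their own route: "All SAEs will be reported as soon as possible to the MoH ethics committee", and they also go to the data monitoring committee. A non-serious grade 3 or 4 event has no individual route to the ethics committee. It is recorded ("All grade 3 or 4, or SAEs and SARs, whether expected or not, should be recorded in the CRF") and reaches the monitoring committee in summaries planned "after 60 and 120 participants have completed the allocated two-week treatment or died", unless that committee asks for more. For such an event, the final comparison by arm is the main place where it would be seen, and that is the table the exclusion touches.

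**Working it through.** **Step 1: does the exclusion reach adverse events?** This is a question of reading.

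- Scope: the population sentence covers all analyses, without restriction to efficacy.
- Alternatives: the per-protocol set is confined to the primary endpoint, and there is no safety set.
- Deferral: the adverse event comparison is specified in the protocol and is not one of the seven outcomes left to the analysis plan.

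So, as worded, the primary adverse event comparison is made in the full analysis population, without patients mistakenly randomised without COVID-19.

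**Step 2: do other sections contradict this?** The secondary endpoint list and the Safety reporting section name which events are compared. Neither says which patients are counted. Only Analysis datasets does that. The sections can be read together without conflict.

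**Step 3: how large could the omission be?** The plan gives no figure to reproduce: it states neither a rate of mistaken randomisation nor an expected adverse event risk. It does give 240 patients randomised 1:1, which is 240 / 2 = 120 per arm. It also requires a positive result "in any specimen <48 hours prior to randomization", so few patients should be affected.

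Assumed for illustration only:

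- k = number of chloroquine patients dropped = 1, 2 or 3
- p = risk per patient of a serious or grade 3 or 4 event = 1%, 5% or 10%

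Formulas, taking patients as independent:

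- share of the arm dropped = k / 120
- chance that at least one patient with an event is omitted = 1 − (1 − p)^k
- expected number of such patients omitted = k × p

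| k | k / 120 | p = 1% | p = 5% | p = 10% |
|---|---|---|---|---|
| 1 | 0.8% | 1.0% | 5.0% | 10.0% |
| 2 | 1.7% | 2.0% | 9.8% | 19.0% |
| 3 | 2.5% | 3.0% | 14.3% | 27.1% |

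The last three columns give the chance of at least one omission. For example, with k = 3 and p = 5%: 1 − 0.95³ = 1 − 0.857 = 14.3%.

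Expected number omitted: from 1 × 0.01 = 0.01 to 3 × 0.10 = 0.30. If the arm had a single patient with an event, the chance that this patient is one of those dropped is k / 120, or 0.8% to 2.5%. With k = 0, which is also plausible, nothing is lost.

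**Step 4: direction.** Infection status at entry precedes randomisation and the rule applies to both arms. Provided mistaken randomisations are identified alike in both arms, the event rates are not biased in expectation.

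**The case against.** The sentence fixes only the primary population. The article says that the analysis will follow a plan completed before database lock, and such a plan commonly defines a safety set. The stated aim is safety and efficacy in patients with confirmed infection, and the secondary objective is the safety profile in COVID-19, so a table of infected patients answers the question asked. Affected patients are also visible elsewhere. A mistaken randomisation is a protocol deviation that must be documented and reported to the trials unit within two days, grade 3 or 4 events are recorded, and the monitoring committee can call for further safety analyses at any time.

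Much of this stands. A supplementary safety set remains possible, a table in confirmed cases is worth having, and oversight of individual patients is largely intact. What does not follow is that the wording needs no change. It is a stated rule on a comparison that the protocol itself specifies, and it makes the narrower set the main one for harms.

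A reader might go further and infer that the exclusion contradicts the endpoint list or the promise to compare all serious and grade 3 or 4 events. The documents do not support that, because those statements concern kinds of event and leave the denominator open. A reader might also infer that the events disappear from the trial record. They do not: they stay in the case report form, and serious ones are reported individually.

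**Conclusion.** The point holds as a minor fault of wording. As written, the main between-arm adverse event comparison omits any patient mistakenly randomised without COVID-19, including one who took chloroquine. Under the assumed ranges, 0.01 to 0.3 affected patients would be missing from the chloroquine arm, with a 1% to 27% chance that at least one is missing. Both the number dropped and the event risk are assumptions, and the entry test makes the low end more likely.

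It would be wrong to conclude that the safety comparison is biased or that no safety set can exist. The exclusion is the same in both arms, and the analysis plan, which is not shown, may add a supplementary set. The reason to act is completeness: with about 120 exposed patients, a single severe toxicity is informative, and no efficacy consideration requires leaving it out.

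**What to change.** In Analysis datasets, restrict the exclusion to efficacy analyses. Then state that the main adverse event comparison includes all randomised participants, whether or not infection was confirmed, by randomised arm. Every randomised participant who received at least one dose of chloroquine is then counted. Any control who received chloroquine should be identified in the table, since analysis by randomised arm alone would not show that exposure.

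Add a supportive adverse event table limited to confirmed COVID-19 cases, to match the secondary objective on safety in COVID-19.

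The cost is a short change of wording and one extra table. No new data, visits or patients are needed, because the events are already recorded, and the sample size is unaffected. The main safety table may then include a few uninfected patients, which the supportive table deals with.
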